### Statistical analysis

Pre-treatment baseline characteristics will be compared between randomized groups to monitor the chance imbalances. Statistical analyses will be performed following the intention-to-treatment (ITT) analysis. The experimental arm (dMRI) will be compared against the control (static MRI) for all primary analysis. We will use chi-squared test for binary outcomes and T-test for continuous outcomes. Spearman’s correlation coefficient will be used to analyze the correlation between the mJOA improvement rate and covariates. A value of *P* < 0.05 will be reported as statistically significant. All analysis will be carried out using SPSS 20.0 software by a researcher blinded to the recruitment and collection.

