#### mJOA

The modified Japanese Orthopaedic Association score (mJOA) is a commonly used research tool in the evaluation of cervical myelopathy. It is comprised of 4 domains that evaluate motor function of the upper and lower extremity, sensory function of the upper extremity and bladder function. Previous studies have demonstrated that the mJOA has the validity of evaluation for CSM patients after surgery [22, 23].

The treating clinical team will evaluate the mJOA score for all CSM patients before surgery. The treating clinicians will not be part of the research team. At 3, 6 and 12 months after surgery, mJOA will be assessed via either outpatient or telephone interview during follow-up. The improvement rate of mJOA score at 3, 6, and 12 months compared to baseline will be calculated finally.

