### Sample size calculation

The sample size is calculated with reference to previous study and based on the sample size calculation formula. The average mJOA score improvement rate of surgical treatment according to static MRI in our hospital was 60.8%. we assume that the mJOA score improvement rate12 months after surgery in group dynamic MRI is 85%. We will recruit a sample of 180 participants including three groups stratified according to the spinal cord compression of static MRI. One hundred and eighty is based on a two-sided t-test, a type I error at 0.025 and type II error at 0.1 after taking into consideration a 1:1 allocation rate and a dropout rate of 20%.

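### The arm comparison on mJOA is an unadjusted t-test that leaves out baseline mJOA as a covariate, the static-MRI group and a joint model of the three visits: valid, but possibly less precise than the data allow

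*Protocol article*

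**What the plan says.** The Statistical analysis section of the protocol article sets the tests by type of outcome: "We will use chi-squared test for binary outcomes and T-test for continuous outcomes". The analysis is to follow intention to treat. Covariates appear once, in a Spearman coefficient that "will be used to analyze the correlation between the mJOA improvement rate and covariates". That describes association and does not adjust the arm comparison.

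The mJOA section makes the score a primary outcome and states: "The improvement rate of mJOA score at 3, 6, and 12 months compared to baseline will be calculated finally". It gives neither a formula for the rate nor the maximum of the scale. Table 2 schedules mJOA at admission and at 3, 6 and 12 months.

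The Sample size calculation section plans on the rate at 12 months: 60.8% with static MRI against an assumed 85% with dynamic MRI. It uses a two-sided t-test with "a type I error at 0.025 and type II error at 0.1", 1:1 allocation and 20% dropout. It also says: "We will recruit a sample of 180 participants including three groups stratified according to the spinal cord compression of static MRI". The Randomization section mentions only the 1:1 ratio, so the document does not show whether allocation itself is stratified by MRI group.

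**The concern.** Three pieces of information are collected on every patient and left out of the stated comparison: baseline mJOA as a covariate, the compression group A/B/C, and the correlation between visits. Where such variables predict the outcome, adjusting for them usually narrows the confidence interval at no cost in patients or visits. The protocol describes its sample as stratified by MRI group, so leaving that group out of the analysis is hard to justify from its own text.

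The improvement rate adds a second difficulty. If it is a ratio with baseline mJOA in the denominator, one mJOA point counts differently from patient to patient, and a t-test on the ratio takes no account of this. At stake is the precision of the main clinical comparison and how far it depends on the mix of baseline severities.

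**Working it through.** **The plan's own figure.** N = 180 cannot be reproduced directly: the section says the number is "based on the sample size calculation formula" but gives no SD. Solving backwards:

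- Evaluable per arm: 180 × 0.8 / 2 = 72.
- Difference: 85 − 60.8 = 24.2 percentage points.
- SD = 24.2 / [(2.241 + 1.282) × √(2/72)] = 24.2 / 0.587 = 41.2 points (two-sided 0.025, 90% power).

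**What adjustment could give on a fixed scale.** If the covariates have multiple correlation R with the analysed outcome, the residual variance is multiplied by 1 − R². With SD 41.2, 72 per arm and two-sided 0.025:

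| R (assumed) | 1 − R² | Power, 24.2-point effect | N for 90% power | Power, 12.1-point effect |
|---|---|---|---|---|
| 0 | 1.00 | 90.0% | 180 | 31.6% |
| 0.3 | 0.91 | 92.7% | 166 | 34.6% |
| 0.5 | 0.75 | 96.6% | 136 | 41.8% |
| 0.7 | 0.51 | 99.6% | 94 | 58.9% |

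The document gives no R, so the gain runs from nil to large.

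**Rate against score.** All simulation inputs are assumptions: 72 per arm, maximum score 17 or 18, and rate = (post − pre)/(maximum − pre).

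- *Benefit of 1 mJOA point, residual SD 1.8 points, baseline mean 11 to 13 (SD 2.6), two-sided 0.05.* Power is 70–81% for the t-test on the rate and 84–90% for ANCOVA on the 12-month score. The gain is about 7 to 15 percentage points.
- *Effect of 15 points and constant SD, both on the rate scale, two-sided 0.05.* The order reverses. With SD 30 the t-test on the rate has 78% and ANCOVA on the score 74% (84% against 74% if scores are not capped at the maximum). With SD 41 it is 52% against 47%. With capped scores the loss is about 3 to 6 percentage points.
- *Effect of 24.2 points on the rate but residual SD constant at 1.8 mJOA points, baseline SD 2.5, two-sided 0.025.* The figures are 52% against 95% (maximum 17, mean 12), and 98.7% against about 100% (maximum 18, mean 10).
- *Adding baseline mJOA to a model of the rate* changes power by at most about 2 percentage points. Nearly all the gain above comes from changing the scale.
- *Under the null*, the t-test on the rate rejected in 1.7% to 2.5% of runs at 0.025, so type I error is not inflated.

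**Weight of a single point.** With gain over room left, one mJOA point is worth 100/(maximum − baseline). At baseline 6 that is 100/11 = 9.1 (maximum 17) or 100/12 = 8.3 (maximum 18) percentage points. At baseline 15 it is 100/2 = 50 or 100/3 = 33. With gain over baseline the order reverses: 100/6 = 16.7 at baseline 6 and 100/15 = 6.7 at baseline 15.

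**The case against.** The strongest reply is that an unadjusted t-test is valid in a randomised trial, that the rest is a preference, and that the document cannot show a gain. Much of this stands. The simulation that favours ANCOVA assumes constant noise in mJOA points. That fits poorly with the planning figure: from baseline 12 on a 17-point scale, 85% recovery gives a mean of 12 + 0.85 × 5 = 16.25, only 0.75 below the ceiling. On the rate scale in which the protocol plans, the advantage can reverse.

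Four stronger readings are tempting, and the text does not support them:

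- *Near-normal patients dominate the result.* This needs the gain-over-room-left formula, which is not stated. That form is the more plausible one: with gain over baseline, 85% would take anyone starting above 17/1.85 = 9.2 or 18/1.85 = 9.7 past the full score. Even so, the effect depends on case mix. In simulation, patients within 3 points of the maximum were 27% of the sample and 72% of the within-arm sum of squares (maximum 17, mean 12), but 4% and 20% with maximum 18 and mean 10. Eligibility sets no mJOA limits, but all patients have a surgical indication and the share of mild cases is unknown.
- *Baseline and the earlier visits are ignored.* The rate is built from baseline, and it is calculated at each visit. What is absent is covariate adjustment and a joint model.
- *The result will be complete-case under an ITT label.* The protocol states ITT and does not state a complete-case rule. Handling of missing data may sit in a document not shown.
- *Adjustment is free power.* It is not free if the endpoint scale changes, and its size is unknown.

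The reply does not remove the core point. The protocol names the method, so this is not a detail left open, and the method leaves out covariates the trial already collects, including a grouping it calls a stratification.

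**Conclusion.** The point holds as one of precision. The stated comparison is an unadjusted t-test without baseline mJOA as a covariate, without MRI group A/B/C and without joint modelling of the visits. It is valid, and no bias or excess of false positives follows from it.

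The size cannot be fixed from the document. The direction depends on whether effect and variability are roughly constant in mJOA points or in percent, and the protocol has no data on this. The gain of 7 to 15 percentage points and the loss of a few points both rest on an assumed formula, maximum score, baseline distribution and residual SD. The table by R rests on an SD solved back from N = 180. The change is worth making because it uses data already planned and would stop the primary estimate depending on an undefined ratio.

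**What to change.** 1. Name 12 months as the primary time point in the Statistical analysis section, in line with the sample-size section.
2. Replace the t-test on mJOA with a prespecified model adjusted for baseline mJOA and static-MRI group A/B/C. A repeated-measures model of mJOA at 3, 6 and 12 months is preferable, with arm, visit and arm-by-visit terms, reporting the adjusted 12-month difference with its confidence interval. Patients with only earlier visits then still contribute.
3. State the formula for the improvement rate and the maximum score. Report the rate as a supportive measure, which keeps the link to 60.8% and 85%.
4. If the sponsor keeps the rate as primary, adjust it at least for MRI group and baseline mJOA, while expecting little from the baseline term.

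Cost: no extra patients or visits. It is more than a change of wording, however. The primary estimate would be in mJOA points rather than percent, so the effect, SD and sample size should be restated on that scale.

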**Discussion:**

This study will help us to explore the indication of dynamic MRI and the value of dynamic MRI in the treatment of CSM, especially the surgical decision making. Dynamic MRI can be a useful tool in the treatment of CSM patients.

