#### Feasibility research

Static MRI will be performed for all patients with CSM who are going to receive surgery. There are three levels of spinal cord compression, incomplete dura compression (Group A, the signal of CSF is still visible), complete dura compression (Group B, no CSF signal and no shape change of spinal cord) and spinal cord compression (Group C, shape change of spinal cord). All participants will be assigned to three groups (A, B, C) based on their static MRI and receive dMRI after consent. The compression degree and T2 high-intensity signal (T2-HIS) on those two MRI will be collected for statistical analysis.

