#### Validation research

The professional surgeon will make two surgical plans for each participant according to the static MRI and dMRI, respectively. Then we will randomly choose one via a random number system to perform. Follow-up will be maintained at 3, 6 and 12 months after surgery including modified Japanese Orthopaedic Association score (mJOA), SF-36 score, 10-s G&R and 10-s step test, frontal and lateral radiography of cervical spine and complications.

Finally, we will statistically analyze the difference between static MRI and dynamic MRI to explore the indication of dMRI for CSM patients in the feasibility research. The validation research aims to identify the clinical effectiveness of dMRI in the treatment of CSM patients, especially the surgical decision making.

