### Randomization

Patients will be recruited from outpatient and eligible participants will be enrolled in the study after informed consent. The treating surgeon will also confirm the eligibility before making two surgical plans based on the static MRI and dMRI, respectively. A researcher will randomly choose one from the two surgical plans via a random number system. Randomization of experiment group (dMRI) and control group (static MRI) will be on a 1:1 basis.

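### The static-MRI groups A, B and C are declared as strata but have no stated role in the randomisation or the arm comparison, and no stated analysis shows whether the clinical effect of dMRI-based planning differs between them

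*Protocol article*

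**What the plan says.** - **Groups.** Feasibility research: "All participants will be assigned to three groups (A, B, C) based on their static MRI and receive dMRI after consent". Sample size calculation: "We will recruit a sample of 180 participants including three groups stratified according to the spinal cord compression of static MRI". The number of patients per group is not given.
- **Allocation.** Randomization has a researcher choose between the two surgical plans with a random number system: "Randomization of experiment group (dMRI) and control group (static MRI) will be on a 1:1 basis". No stratification factor or blocking is named.
- **Arm comparison.** Statistical analysis: "The experimental arm (dMRI) will be compared against the control (static MRI) for all primary analysis". The named tests are chi-squared for binary and t-test for continuous outcomes. No group term, stratified test, subgroup analysis or interaction is mentioned.
- **Covariates.** The same section adds that Spearman's "correlation coefficient will be used to analyze the correlation between the mJOA improvement rate and covariates". The covariates are not named.
- **Indication aim.** The Discussion part of the abstract says "This study will help us to explore the indication of dynamic MRI". Validation research assigns that aim to the imaging comparison: "we will statistically analyze the difference between static MRI and dynamic MRI to explore the indication of dMRI for CSM patients in the feasibility research". Feasibility research names the data: "The compression degree and T2 high-intensity signal (T2-HIS) on those two MRI will be collected for statistical analysis". The main Discussion repeats the assignment and ends by hoping for treatment individualised by dMRI.

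**The concern.** Group is known before randomisation, defines the structure of the trial and may well be prognostic. A factor of that kind is normally used in allocation and then in the model. The text says the sample is stratified by it, but neither the section on allocation nor the one on analysis does anything with it.

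The validation part also asks whether planning surgery from dMRI improves outcome. If the result is to guide individualised planning, a reader will want to know whether the dMRI-minus-static difference in mJOA improvement varies over A, B and C. That is an arm-by-group question. A correlation of outcome with covariates answers a different one, namely who does well, whatever the arm.

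At stake are balance within the groups, some precision in the main comparison, and a sound basis for any statement about groups. The validity of the overall randomised comparison is not at stake.

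**Working it through.** **Inputs from the protocol article:** 180 randomised 1:1; 20% dropout; three groups; mJOA improvement rate 60.8% (static) against 85% (dMRI), a difference of 24.2 points; two-sided t-test, type I error 0.025, type II error 0.1.

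**Assumptions:** equal groups of 60, since sizes are not stated. Evaluable patients are 180 × 0.8 = 144, so 72 per arm, 48 per group, and 24 per arm within a group. The SD is not stated. The value that makes 180 fit the stated t-test is 24.2 / [(2.241 + 1.282) × √(2/72)] = 41.2 points. I use 30 to 41.2 points as a range.

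**1. Balance within a group if randomisation is simple.** For n = 60, P(X ≤ 24 or X ≥ 36) with X ~ Binomial(60, 0.5) is 0.155, about 16%. For smaller groups, the chance of 60:40 or worse is 27% (n = 40) and 50% (n = 20). With three groups of 60, at least one is that unbalanced in 1 − (1 − 0.155)³ = 40% of trials.

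**2. What a Spearman correlation with group measures.** Simulation over both arms (3,000 runs, 48 evaluable per group, SD 40 points):

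| Scenario | Effect in A/B/C | Prognostic shift in A/B/C | Mean rho | Significant |
|---|---|---|---|---|
| Same benefit everywhere | 24.2 / 24.2 / 24.2 | 0 / −15 / −30 | −0.28 | 94% |
| Benefit rises by group | 0 / 24.2 / 48.4 | 0 / −12.1 / −24.2 | 0.00 | 3% |

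The second scenario is constructed: prognosis is set to cancel the average trend. Without such cancellation Spearman can be significant too (88% in a run with effects −20/0/+20 and SD 30). So the percentages are illustrations. What they show is that a correlation over both arms cannot separate prognosis from differential benefit.

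**3. Precision of the group-specific results.**
- Overall SE: SD × √(2/72) = 5.0 points (SD 30) to 6.9 (SD 41.2).
- Within one group: SD × √(2/24) = 8.7 to 11.9 points. Ratio to overall: √3 = 1.73.
- Contrast of two groups' effects: SD × √(4/24) = 12.2 to 16.8 points. Ratio to overall: √6 = 2.45.
- Power for a 24.2-point difference in effect between two groups, two-sided 0.05: Φ(24.2/12.25 − 1.96) = 51% at SD 30; Φ(24.2/16.82 − 1.96) = 30% at SD 41.2.

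**The case against.** The strongest reply is that the protocol does not use the Spearman analysis to find the indication for dMRI. Validation research and the main Discussion give that aim to the comparison of static with dynamic images in the same patient. That comparison asks in whom dMRI shows something static MRI does not, and needs neither randomisation nor an interaction. This stands. A reader might infer from Statistical analysis that prognostic factors will be reported as indications, or that the indication question cannot be answered. The text supports neither: it never says how the correlation will be interpreted, names no covariates, and does not say that the arms are pooled.

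Second, an article may leave blocking, strata and subgroup analyses to the full protocol or SAP. The word in Sample size calculation could mean stratified recruitment or stratified randomisation. This stands in part: simple randomisation is a possibility, not a stated fact, so the 16% is conditional on it. But the article names its tests for the arm comparison, and those ignore group. If allocation is in fact stratified, a t-test without group gives up precision whenever group is prognostic.

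Third, group sizes and SD are assumed, and group-specific estimates will be imprecise. That is true, and is why they belong among exploratory results.

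**Conclusion.** The point holds in a limited form. A, B and C are declared as strata, yet the sections on allocation and analysis give them no role. No stated analysis shows whether the clinical effect of dMRI-based planning differs by group. The imaging comparison shows where the two scans differ, which is not the same as in whom acting on dMRI improves outcome. The Spearman result can be reported as prognostic description only.

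This is a nearly free improvement, not an error that undermines the trial: the overall arm comparison remains valid. The stronger conclusion, that the trial assigns its indication aim to an unsuitable correlation, is not supported by the document.

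The 16% imbalance figure rests on simple randomisation and groups of 60. The precision ratios of 1.7 and 2.4 rest on equal groups. The 30% to 51% power rests on SDs of 41.2 to 30 points, 24 evaluable patients per arm in each group, and a normal approximation.

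**What to change.** 1. **Randomization:** state that the 1:1 draw is made in permuted blocks within A, B and C. If it already is, one sentence settles it.
2. **Statistical analysis, primary:** replace the unadjusted arm comparison of mJOA improvement rate with a linear model containing arm and group.
3. **Statistical analysis, exploratory:** report the dMRI-minus-static difference with its CI in each group, plus the arm-by-group interaction. State that a non-significant interaction is not evidence of equal benefit.
4. **Spearman:** describe it as prognostic, and not as showing who benefits from dMRI.

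The cost is three randomisation lists in place of one and a few model terms, with no extra patients or visits. If recruitment has begun, item 1 can apply only to later patients, while items 2 to 4 remain open until the data are unblinded. The group-specific estimates will be imprecise and must be labelled so.

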## Discussion

We have presented the rationale and design of a prospective randomized controlled trial on the therapeutic value of dMRI in CSM patients, especially the surgical decision making. The RCT introduced here includes feasibility and validation research. The feasibility research will compare dynamic MRI with static MRI and explore the indication of dMRI for CSM patients. The validation research will identify the clinical effectiveness of dMRI in the treatment of CSM, especially the surgical decision making.

The long-term follow-up of radiographic outcomes, nerve function recovery and quality of life will provide more evidence about the clinical use of dMRI in the treatment of CSM.

As is noted in some studies, there are many patterns or more cord compression on dMRI of CSM patients which are usually invisible on static MRI and it is significant for the diagnosis and prognostic evaluation for CSM patients [10, 13, 15, 31]. For instance, a prospective study of 50 patients showed that cervical cord available space (CCAS) was greater in the neutral position than in either extension or flexion. The T2-HIS was more evident in flexion position (20/50) than in neutral position (13/50) and in extension (7/50) [10]. Another study demonstrated that higher stages of spinal cord compression were found in the extension position compared with the stage in the neutral and flexion positions. Better visualization of T2-HIS was also found on flexion position [15]. Typically, the T2-HIS and degree of compression on MRI images may reveal the severity of damage of spinal cord [32]. A study shows that the preoperative and postoperative evaluation of CSM patients were better in the patients with no T2-HIS compared with patients with T2-HIS [24]. The specific patterns on the extension and flexion position is a possible reason why there are some patients with negative image findings but still suffer from myelopathy symptoms.

Up to now, limited studies focused on the surgical decision made by dMRI. Two studies of dMRI just mentioned it may be helpful for CSM patients to determine the surgical management by dMRI [8, 15]. Two studies [11, 19] used dMRI in preoperative planning to determine potential levels for decompression. In 1 study [11], upon reviewing the dMRI results, the number of potential levels needing decompression was significant increased by 3 of 4 reviewers with an inter-rater correlation coefficient of 0.81 by dMRI higher than 0.67 by normal MRI. In the other study [19], they had selected the levels requiring decompression with a preoperative dynamic MRI. There was no significant difference of function recovery rate between selective laminoplasty by dMRI and nonselective laminoplasty. This study suggested that a selective decompression based on the preoperative dynamic MRI was clinically useful. However, those studies just focus on the selection of decompression levels and there are also some other factors such as the severity of compression, surgical approach and selection of implants, which should also be taken into consideration when a surgical plan for CSM is made.

Dynamic MRI may play a significant role in the treatment of CSM while there is no enough clinical evidence. The RCT introduced here will have a long period of follow-up after surgery (12 months), comprehensive CSM outcomes, calculated sample size and two stages of research to provide more evidence for clinical effectiveness of dMRI in the treatment of CSM. This new design will help us to modify the surgical decision making of CSM and draw individualized therapeutic schedule for CSM patients according to dMRI.

